The mechanism of action and the safety profile make PEA an appealing choice for pain relief in older people. However, the evidence base for its efficacy to treat chronic pain in the elderly is not fully convincing. In addition, formulations containing um-PEA, like *Normast®*, are available in Italy only out-of-pocket and a treatment cycle at the doses recommended by the product information sheet would cost the patient about € 60. Given that the required treatment for persistent pain would probably be longer, the cost should be balanced by the actual effectiveness. These reasons represented the rationale to adopt a randomized *N*-of-1 trial as a more objective and personalized prescribing approach, compared with the conventional trial (i.e. ‘prescribe and see’) [39]. In general, *N*-of-1 trials are within-patient randomized multi-period crossover trials to compare, in a double-blind fashion, therapeutic strategies (e.g. an active drug versus no treatments, or two different active therapies), with time periods as randomization units and the patient as control for herself or himself. This study design can be theoretically used to test new drugs along their way to marketing authorization. In our case, we will adopt this approach to determine the best therapeutic choice for a certain patient in clinical practice, objectively and empirically, with randomization and blindness as instruments to overcome those factors (e.g. natural history of the disease, ‘placebo effect’, expectations) that might bias conventional trials of therapies [39–41]. In particular, the series of *N*-of-1 trials on PEA for chronic pain in older patients will be part of the activity of the Geriatric *N*-of-1 Service, an experimental project that we have implemented, with the approval of the local ethical committee, following the pioneering experience of Guyatt and colleagues [42] but in the specific context of geriatric medicine, which suffers most from the limits of parallel group randomized controlled trials, the current paradigms of evidence-based medicine [43].

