### Allocation and blinding

The sequence will be generated by the pharmacist using the web site www.randomizer.org. Two sets of two random numbers (numerals 1 [arbitrarily designated as placebo] or 2 [designated as active]), with each number in a set remaining unique, will be generated for each patient. Pharmacists will be recording the allocation sequence and will provide the study drug (either active drug or placebo, indistinguishable) to the clinical investigators at the beginning of each study period. Patients, participating caregivers, treating physicians, and clinical investigators (responsible for outcome assessment and data analysis) will be blinded to the treatment sequence.

Unblinding will be permissible at any time that the trial will be considered concluded. Reasons for which the trial will be deemed concluded other than its completion will be: the patient withdraws consent; the patient or the treating physician is convinced that drug effectiveness has been established or refuted before the end of the designed trial; and safety concerns.

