### Sample size

For each *N*-of-1 trial, the sample size is represented by the number of periods of treatment. The choice to design each trial including two treatment pairs is not based on a formal power calculation, considering that *N*-of-1 trials with a practicable number of pairs can rarely reach the conventional level of statistical power of 80–90 % [54]. The choice is a trade-off between the desire of a trial as powerful as possible, and the practical need to limit its duration, given the required length of each period and of the washout between each treatment period. However, considering the actual objective of each *N*-of-1 trial, two treatment pairs seem a reasonable choice, given the starting good level of confidence on the treatment effectiveness that our geriatric team derived from the brief experience with the product (based on conventional trials) we preliminarily had in our practice.

A meta-analysis of the performed *N*-of-1 trials to estimate an overall population treatment effectiveness and evaluate the possible determinants of the effect heterogeneity between trials will be a proof-of-concept study. Given the explorative nature of this secondary objective, the number of *N*-of-1 trials that will be meta-analyzed is not dictated by a specific sample size calculation. A first meta-analysis will be performed on those completed *N*-of-1 trials initiated during the first 12 months from the start of the first *N*-of-1 trial, as long as there are at least three trials. A second meta-analysis will be performed including all the *N*-of-1 trials initiated within 24 months from the start of the first *N*-of-1 trial (study duration).

The posterior probability that um-PEA is better than placebo for a certain patient (single trial) and for the population (trial series) will be provided through a Bayesian approach.

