#### Meta-analysis of N-of-1 trial series

A linear mixed effect model [56] will be performed, with the week mean pain intensity score or the week impact-on-function score as dependent variable and the patient included as random effect (random intercept). The primary analyses will include treatment as the single explanatory variable with fixed effect. Secondly, a random coefficient for treatment (i.e. treatment effect varying between patients) will be tested. A random intercept for pair, in a nested structure (outcome measures within patients, and patients within pairs) will also be tested. A possible residual carryover effect (>2 weeks) will finally be tested, including sequence, pair, treatment by sequence interaction, and treatment by pair interaction as fixed-effects. The models will be also repeated excluding the first week measures of each period.

Patient-level (or study-level) variables will also be tested in the analyses as possible explanatory variables of treatment effect heterogeneity.

In addition to the classic (frequentist) analysis, results of the individual trials and their combination will be approached using Bayesian hierarchical methods, as described by Zucker et al. [57]. Non-informative priors will initially be modeled. In addition, physician’s pre-trial confidence in treatment effectiveness will be used to model informative priors.

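### The primary pooled model has no period term, so shared change in pain within a treatment pair shifts the realised um-PEA estimate when treatment orders are unequal, and shared change between pairs only widens its interval

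*Protocol article*

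**What the plan says.** The Protocol article, under Meta-analysis of N-of-1 trial series, plans a linear mixed model "with the week mean pain intensity score or the week impact-on-function score as dependent variable", with a random intercept for patient. It then fixes the fixed part: "The primary analyses will include treatment as the single explanatory variable with fixed effect".

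Time appears only in later models, and only through pair. One is "A random intercept for pair, in a nested structure". The last is a check for carryover, "including sequence, pair, treatment by sequence interaction, and treatment by pair interaction as fixed-effects". No model names period or week as an adjustment.

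Under Allocation and blinding, each patient's order comes from "Two sets of two random numbers (numerals 1 [arbitrarily designated as placebo] or 2 [designated as active]), with each number in a set remaining unique". Order is thus random within each pair, and no balancing of orders across patients is stated. Under Sample size, the first pooled analysis goes ahead "as long as there are at least three trials".

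**The concern.** Each pair contains both treatments, but one of them always comes first. If pain tends to fall between the two periods of a pair in all patients, placebo-first pairs flatter um-PEA and um-PEA-first pairs penalise it. These errors offset only if the two kinds of pair are equally common. With orders drawn independently and few trials, they usually are not. The primary model has no term to take up the difference.

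Some shared change is plausible: patients enter complaining of pain that may fluctuate, and a run-in is not routine. The Background relies on randomisation and blinding "to overcome those factors (e.g. natural history of the disease" and similar influences). In a small series randomisation does that on average, not in the series obtained. At stake is the average um-PEA effect, which is the research objective and is meant to inform decisions for patients outside the trials. The same model serves the function score.

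**Working it through.** **Inputs from the protocol.** Four periods of 3 weeks and three washouts of 2 weeks give 4 × 3 + 3 × 2 = 18 weeks, which reproduces the stated duration. On-treatment weeks are 1-3, 6-8, 11-13 and 16-18 (midpoints 2, 7, 12, 17). Each patient gives 12 week means, six per treatment, and the four orders are equally likely.

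**Assumptions not in the protocol.** Complete trials, on-treatment weeks only, no carryover, no um-PEA effect, independent weekly errors with SD 0.7-1.0, two-sided 5% level, and the drift shapes below. With complete data, treatment is balanced within patient, so the random-intercept estimate equals the within-patient difference.

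**Step 1: shift by order.** The linear column is mean week on um-PEA minus mean week on placebo, to be multiplied by the weekly slope. The next column is for a fall of D points after period 1 (negative favours um-PEA).

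| Order | Linear drift (weeks) | Fall D after period 1 | Level change between pairs |
|---|---|---|---|
| um-PEA first in both pairs | (2+12)/2 − (7+17)/2 = −5 | +D/2 | 0 |
| um-PEA first in pair 1 only | (2+17)/2 − (7+12)/2 = 0 | +D/2 | 0 |
| placebo first in pair 1 only | 0 | −D/2 | 0 |
| placebo first in both pairs | +5 | −D/2 | 0 |

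Only change within a pair shifts the estimate.

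**Step 2: imbalance in a realised series.**
- With n trials the linear shift is 5 × (placebo-first − um-PEA-first pairs)/2n weeks, with root mean square 5/√(2n): 2.04, 1.12 and 0.79 weeks at 3, 10 and 20 trials.
- A 2-point fall from week 1 to week 18 is 2/17 = 0.118 points per week. The typical shift is then 0.24, 0.13 and 0.09 points, with a maximum of 5 × 0.118 = 0.59.
- With three trials, exact balance has probability C(6,3)/2⁶ = 20/64 = 31%.
- With 10 trials, a split of pair-1 orders of 7:3 or worse has probability 2 × (120+45+10+1)/1024 = 34%. At 7:3 placebo-first, the shift is (3−7)/10 × D/2 = −0.2D: 0.2 to 0.4 points in favour of um-PEA for D of 1 to 2.

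**Step 3: does the model's standard error cover this?** Its squared standard error is (residual variance)/(3n). Shared change adds about (within-patient sum of squares)/11 to the residual variance.
- *Linear.* Sum of squares 3 × (7.5² + 2.5² + 2.5² + 7.5²) + 4 × 2 = 383 week². The model adds 383/11/3n = 11.6/n. The true added variance is (25+0+0+25)/4/n = 12.5/n. These nearly agree, so the error rate stays nominal but precision is lost.
- *Fall after period 1.* Sum of squares 12 × ¼ × ¾ × D² = 2.25D². The model adds 0.068D²/n; the truth is 0.25D²/n. The added variance is understated about 3.7-fold.
- *Change of D between pairs.* Sum of squares 3D². The model adds 0.091D²/n; the truth is 0. The interval is too wide.

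Example: 20 trials, SD 0.7, D = 2 after period 1. True SD = √(0.49/60 + 0.25 × 4/20) = 0.241; model standard error = √(0.49/60 + 0.068 × 4/20) = 0.148. The 1.96 cut-off then acts like 1.96 × 0.148/0.241 = 1.20, a false-positive rate of about 23%.

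**Step 4: simulation, series of no more than 20 trials.** Treatment-only false positives:

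| Shared change | Rate |
|---|---|
| Linear fall | about 4-6% |
| 2-point exponential fall (4-week constant) | about 8-13% |
| 1-point drop after period 1 | about 10-16% |
| 2-point drop after period 1 | about 18-25% |
| 2-point change between pairs | 0-0.6% |

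With period added the rates are about 3-6%. At 20 trials and SD 0.7, adding period cuts the true SD of the estimate from 0.124 to 0.091 (linear 2 points) and from 0.237 to 0.091 (2-point drop after period 1).

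**The case against.** Several counter-arguments stand, and they set the limits of the point.

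- A reader might infer that any shared change in pain biases the um-PEA estimate. It does not. A level change between pairs cancels in every complete trial and makes the test conservative.
- A reader might also infer that a false-positive rate of 10-25% is to be expected. Those figures need pain to stay flat through period 1 and then drop. If the same 1-point fall comes after week 1, the rate is 4.3-5.5%; a 1-point exponential fall gives 5-9%. The documents give no size or shape for any drift. They set no minimum pain intensity at entry, require pain of at least six months, and bar new or changed pain therapy around enrolment, all of which argues against a large shared fall.
- Randomisation does make the estimate unbiased over repeated series, as the Background intends.
- The later models help in part: a pair intercept takes up level differences between pairs, and the treatment-by-sequence term overlaps with period within pair. They are secondary, the last is a carryover test, and neither changes the primary estimate.
- A four-level period factor is not free in the smallest permitted series. At three trials with no drift and SD 0.7, it raises the SD of the estimate from about 0.23 to 0.30.

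**Conclusion.** The point holds in limited form. The protocol states the model outright, so this is not a detail left to an analysis plan. Shared change within a pair shifts the realised um-PEA estimate when orders are unequal, and otherwise goes to its error; shared change between pairs costs only precision. The claim that the planned estimate is biased in general is not supported.

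The size rests on assumed drift and residual SD. It runs from lost precision with a nominal error rate (linear fall) to 10-25% false positives (worst case, a 1-2 point drop after period 1). The pooled analysis is a secondary, exploratory objective and the individual treatment decisions do not use this model, so the weight is moderate to minor. The low cost of the remedy is the main reason to act.

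**What to change.** In the primary pooled model for both pain and function, add period (1-4, categorical) as a fixed effect beside treatment and the patient random intercept. Report the period-adjusted treatment contrast as primary and keep the treatment-only model as a sensitivity analysis.

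For very small series (about 3-5 trials), pre-specify a linear week term instead, with the cut-off fixed in advance. At three trials the four-level factor cannot be fitted if all three share one order (4 × (1/4)³ = 1/16). With SD 1 and a 2-point linear fall at three trials, the linear term lowers the standard error from 0.40 to 0.34, while the four-level factor gives 0.41. A linear term removes a steady trend but only part of an abrupt drop, and the report should say so.

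The cost is one or two sentences, no new data, up to three degrees of freedom, and some precision if there is no shared change. With SD 0.7 and the four-level factor, the SD of the estimate goes from 0.180 to 0.207 at 5 trials, 0.127 to 0.136 at 10, and 0.090 to 0.092 at 20.

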### Study objectives

The primary (clinical) objective of our study is to apply the *N*-of-1 trial approach to test the effectiveness of um-PEA 600 mg (*Normast®*) twice a day for chronic pain in a certain patient referring to our geriatric unit in whom the treatment might be indicated, and to assist decisions on long-term treatment of that patient.

As a secondary (research) objective, we aim to obtain an overall estimate of the effectiveness of um-PEA 600 mg twice a day compared with placebo and evaluate the possible determinants of between-trial heterogeneity, through a meta-analysis of the *N*-of-1 trials performed for clinical purposes. Contextually, a classical frequentist meta-analytical approach will be compared with a Bayesian approach, and the potentialities of a Bayesian-based cumulative study design explored.

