### Study design

Each trial will be a blinded placebo-controlled randomized trial. Each trial’s duration will be 18 weeks, comprising two um-PEA and placebo treatment pairs assigned in a random order according to a pairwise randomization scheme. Thus, the sequence of each pair can be either um-PEA/placebo or placebo/um-PEA. Each treatment period will last 3 weeks. The treatment periods of each pair and the two pairs will be separated by 2-week washout intervals to minimize carryover effects. A run-in period will not be routinely performed, but will be considered when deemed appropriate (for example, in case of history of allergies to drugs or drug excipients). Figure 1 summarizes the schedule for the intervention and washout periods.

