#### Eligibility criteria for participants

Older patients complaining of chronic pain of likely osteoarticular or neuropathic origin will be eligible for the study. Detailed *inclusion criteria* are:Patient age ≥ 65 years.Pain is localized at the back (any level) or at the joints or at the limbs.The pain is chronic, i.e. it has been present for at least 6 months, even if with fluctuations.The pain is attributable to one or more of the following conditions: osteoarthritis or osteoarthrosis; spondylosis; radiculopathy; diabetic peripheral neuropathy; post-herpetic neuralgia; chronic idiopathic axonal polyneuropathy; fibromyalgia; or pain of uncertain origin or idiopathic, as long as it has had and it is expected to have a chronic nature, even if with spontaneous fluctuations.The treating physician deems PEA to be a possible treatment option for the patient, either alone or as an add-on medication on top of other analgesic drugs.

Dealing with geriatric patients, and willing to offer the opportunity of a treatment option with an objective and empirical evaluation regardless of patient cognitive integrity, we will distinguish two cases:Case 1 (self-assessment): The patient is able to give an informed consent and to express the characteristics of the pain-like intensity and impact on function over a quantitative scale; the patient might be able to self-compile questionnaires, or to reliably answer questions administered by a caregiver.Case 2 (caregiver-based-assessment): The patient has a certain degree of cognitive decline that hinders the direct involvement of the patient in the consent process or in the outcome self-assessment, but an all-day caregiver willing to collaborate and consent to the trial is present. In this case, the pain has to be clearly expressed by the patient in a modality that can be assessed in its frequency and impact on function by someone other than the patient.

*N*-of-1 trials on case 1 patients will be candidates for the secondary objective of our study. The opportunity to meta-analyze case 2 trials will be judged according to the number and heterogeneity of the assessment instruments and modalities of completed trials.

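### The pooled test of whether the um-PEA effect differs between patients has no period-level error term, so correlated weekly scores within a period would be read as patient-to-patient differences

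*Protocol article*

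**What the plan says.** The dependent variable of the pooled linear mixed model is "the week mean pain intensity score or the week impact-on-function score" (Meta-analysis of N-of-1 trial series). The primary model has a patient random intercept and treatment as its only fixed effect. The next step is the heterogeneity test: "Secondly, a random coefficient for treatment (i.e. treatment effect varying between patients) will be tested". A third random term follows: "A random intercept for pair, in a nested structure (outcome measures within patients, and patients within pairs) will also be tested". I read this as pair within patient, since pairs belong to patients. Sequence, pair and their interactions with treatment enter later as fixed effects, and the models are repeated without the first week of each period.

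On the design, the Background describes N-of-1 trials "with time periods as randomization units and the patient as control for herself or himself". Study design gives two pairs per patient and says "Each treatment period will last 3 weeks". Each patient therefore has four periods, two per treatment, with three weekly values in each. Study objectives makes it part of the secondary objective to "evaluate the possible determinants of between-trial heterogeneity, through a meta-analysis of the" N-of-1 trials. The eligibility criteria admit fluctuating pain. For pain of uncertain origin the wording is "as long as it has had and it is expected to have a chronic nature, even if with spontaneous fluctuations", and the general definition of chronic pain makes a similar allowance.

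**The concern.** A good or bad spell lasting most of a 3-week period moves all three weekly scores together. With only two periods per treatment, it shifts that patient's um-PEA minus placebo difference. Among the listed random terms, only the treatment coefficient can absorb that shift. A pair contains one period of each treatment, so a pair intercept cancels from the within-pair difference. The treatment interactions are fixed effects common to all patients and cannot represent one patient's bad spell.

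The test can therefore reject because pain fluctuates, even when um-PEA acts identically in everyone or in no one. At stake are the heterogeneity test, the estimated between-patient SD and, through the same error structure, the tests of patient-level variables as determinants.

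**Working it through.** **Figure to reproduce.** The article gives no power, error rate or sample size for this test. The design counts agree with its stated duration: 4 × 3 + 3 × 2 = 18 weeks.

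**Inputs.** From the article: 3 weekly values per period, 2 periods per treatment, a patient intercept with an optional pair intercept, and at least 3 trials for the first meta-analysis. Assumed: period variance sp², weekly variance sw², r = sp²/sw², period intraclass correlation (ICC) = r/(1+r), 3 to 20 trials, and nominal 5%. The P ≤ 0.1 criterion in the article classifies single-trial results only.

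**Mean squares with zero true heterogeneity**

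- A patient's treatment difference averages two periods per arm. Its variance is 2(sp²/2 + sw²/6) = sp² + sw²/3, so the patient-by-treatment mean square has expectation sw² + 3sp².
- The residual within patient and treatment has 5 df. One is between periods, with expectation sw² + 3sp². Four are within periods, with expectation sw². The average is sw² + 0.6sp².
- A pair intercept removes one of the two between-period df per patient. That leaves 9 df with expectation sw² + (3/9)sp² = sw² + sp²/3.

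The ratio of expectations is (1+3r)/(1+0.6r), or (1+3r)/(1+r/3) with pair. It should be 1, and is 1 only if r = 0.

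| Assumption | r | Ratio | Ratio with pair |
|---|---|---|---|
| Period ICC 0.1 | 0.111 | 1.333/1.067 = 1.25 | 1.333/1.037 = 1.29 |
| Period SD half weekly SD | 0.25 | 1.75/1.15 = 1.52 | 1.75/1.083 = 1.62 |
| Equal SDs | 1 | 4/1.6 = 2.5 | 4/1.333 = 3.0 |

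**Simulated false positives, nominal 5%, zero heterogeneity, 3 to 20 trials**

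| Assumption | F test on the listed terms | REML likelihood-ratio test, 50:50 mixture |
|---|---|---|
| Independent weekly values | about 5% | 3–5% |
| Period ICC 0.1 | 8–17% | 6–16% |
| Period SD half weekly SD | 14–38% | 9–35% |
| Equal SDs | 30–86% | 22–85% |
| Weekly AR(1) 0.5, no period effect | 23–70% | 17–69% |

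Rates rise with the number of trials, and repeat simulations agree to about one percentage point. Fitted mixed models also showed inflation, at lower rates: 45–53% with 12 trials and equal SDs, and 29–32% with 15 trials at ICC 0.3. Both had convergence warnings.

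**Do the planned variants help?** At ICC 0.3, adding the pair intercept raises the F-test rate from 38% to 45% with 10 trials and from 58% to 68% with 20. Dropping first weeks lowers these rates to 21% and 31% but does not remove the inflation.

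**Effect on the estimate.** The implied heterogeneity variance is (difference in mean squares)/3. At equal SDs this is (4 − 1.6)/3 = 0.8 sw², an SD of about 0.89 weekly SDs when the truth is 0. The simulated median with 12 trials was 0.84.

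**Corrected test.** Comparing between-patient with within-patient variation of the pair differences, F(J−1, J), rejects about 5% in every scenario above.

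**The case against.** The article states no null hypothesis, test statistic, significance level or residual covariance for this step. A condensed article may leave residual correlation to a fuller plan that is not shown. The eligibility wording on fluctuation gives no time scale, so it does not establish variation shared over three weeks. The meta-analysis is described as exploratory and proof-of-concept. A Bayesian hierarchical analysis is also planned, and its error structure is not given.

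Much of this stands and limits the point. A reader might infer that the false-positive rate is far above 5% whatever the data. The documents do not support that: the rate depends on an unstated variance ratio and number of trials. It is modest, about 6–10%, at ICC 0.1 with 3 to 5 patients, and absent if weekly values are independent. A reader might also infer that a spurious result triggers the search for determinants. It does not, because patient-level variables are to be tested regardless. Nor are individual treatment decisions affected: under Analysis of individual N-of-1 trials they use period means compared within pairs, which is the appropriate unit.

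What does not stand is that this is only missing detail. The article lists its random terms, and the list omits the randomised unit. Applied as listed, the test is valid only if weekly scores are independent given patient, treatment and pair.

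**Conclusion.** The point holds conditionally. The structural result is exact algebra: period variance enters the patient-by-treatment term in full and the residual only in part, and the pair intercept widens the gap. Some within-period correlation is plausible for fluctuating chronic pain, but its amount is not documented. The rejection rates are therefore a range, from nominal under independence to 86% at equal SDs with 20 trials, with somewhat lower rates for likelihood-ratio and fitted mixed-model tests. The 5% benchmark is mine, because the article sets no level for this test. The point concerns the between-patient variance, its test and the determinants analysis. It makes no claim about the standard error of the average effect. The analysis is secondary and exploratory, so the consequence is limited, but heterogeneity is a named objective and the correction is cheap.

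**What to change.** Amend the analysis section as follows:

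- Compute one um-PEA minus placebo difference of period means per pair, and test between-patient against within-patient variation of these differences with F(J−1, J) for J complete trials.
- If a mixed model is preferred, keep both a pair-within-patient and a period-within-patient random effect in the null and alternative models before testing the random treatment coefficient. Period alone is not equivalent: when pairs differ it is conservative, rejecting 0.3–2.2% at nominal 5% in simulation.
- Use the same error structure for the between-patient SD and for tests of patient-level determinants.

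This costs a few sentences and needs no new data or patients. The price is lower power. For a true treatment-effect SD of 1.5 weekly SDs and a period SD of 0.7 weekly SDs, power is about 23%, 53%, 70% and 89% with 3, 8, 12 and 20 trials. With very few trials, heterogeneity should therefore be reported as an estimate with its interval rather than as a test result.

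### The pair random intercept is nested the wrong way round, and the mixed model has no random effect for the randomized period (minor)

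*Protocol article*

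**What the plan says.** The section on meta-analysis of the N-of-1 trial series specifies a linear mixed model "with the week mean pain intensity score or the week impact-on-function score as dependent variable" and "the patient included as random effect (random intercept". In the first step, "The primary analyses will include treatment as the single explanatory variable with fixed effect". A treatment coefficient varying between patients is tested next. Then a random intercept for pair is also to be tested, "in a nested structure (outcome measures within patients, and patients within pairs". A last step tests carryover with sequence, pair and their interactions with treatment as fixed effects. Patient-level variables are also to be tested as sources of heterogeneity.

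The Study design section describes each trial as "comprising two um-PEA and placebo treatment pairs assigned in a random order according to a pairwise randomization scheme", and adds: "Each treatment period will last 3 weeks". The Background describes N-of-1 trials as crossover trials "with time periods as randomization units and the patient as control for herself or himself". No random effect for period appears in any of the models described.

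**The concern.** Two things in the model description do not fit the design.

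- **Order of nesting.** Pairs belong to patients; no patient belongs to a pair. Read literally, pair becomes a top-level factor with two levels, so its variance rests on a single contrast. The patient intercept becomes one intercept per patient-pair combination, and a patient's first and second pair are then treated as unrelated subjects.
- **Missing level.** The period is what is randomized, and each period supplies three weekly means. Without a period term, those three means count as independent replicates of the treatment contrast.

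At stake are the SE of the average effect and the analysis of what drives differences between patients. Both belong to the stated secondary objective. The first meta-analysis may go ahead with as few as three trials.

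**Working it through.** The article gives no SE, power figure or variance component for this model, so there is no figure to reproduce. The check uses the balanced design and assumed variances.

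**Inputs from the protocol article:** 2 pairs per patient, 2 periods per pair, 3 weekly means per period, hence 12 on-treatment values per patient. **Assumed:** n patients; variances W (week), P (period), Q (pair within patient) and S (treatment effect between patients).

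**Formulas** (complete trials; SE² = 4 × MS / (12n), where MS is the error mean square that the model uses):

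- Patient intercept only: MS = W + (6Q + 9P + 3S)/11
- Pair intercept, either nesting order: MS = W + (3P + 1.5S)/5
- Adding a period-within-pair intercept: MS ≈ W + 3P + 1.5S
- True value: SE² = (W/3 + P + S)/n

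The second line is the same for both orders because each pair holds one active and one placebo period. The treatment contrast therefore lies within the patient-pair, and how patient-pairs are grouped above that level does not affect it.

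**Intercept-only comparison, n = 10, week SD 1, S = 0**

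| Period SD | Pair SD | Patient only | Pair intercept, as stated | Pair intercept, corrected order | True |
|---|---|---|---|---|---|
| 0 | 0 | 0.183 | 0.183 | 0.183 | 0.183 |
| 0 | 0.8 | 0.212 | 0.183 | 0.183 | 0.183 |
| 0.8 | 0 | 0.225 | 0.215 | 0.215 | 0.312 |
| 0.8 | 0.5 | 0.235 | 0.215 | 0.215 | 0.312 |

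Restricted maximum likelihood (REML) fits to simulated data (60 series per row) gave the same SE for both orders to within 0.002. With a period-within-pair intercept, the simulated SE was 0.300 and 0.307 in the last two rows. With three trials and period SD 0.8, no pair variance, the SE is 0.392 in either order against a true 0.570.

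**With effect heterogeneity, n = 10:** effect SD 0.7, period SD 0.5, pair SD 0.5, week SD 0.8, so S = 0.49, P = 0.25, Q = 0.25, W = 0.64.

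- True: √[(0.213 + 0.25 + 0.49)/10] = √0.0953 = 0.309. Heterogeneity contributes 0.049 of 0.0953, or 51%; period contributes 0.025, or 26%.
- Patient only: MS = 0.64 + (1.5 + 2.25 + 1.47)/11 = 1.115; SE = √(4 × 1.115/120) = 0.193.
- Pair intercept, either order: MS = 0.64 + (0.75 + 0.735)/5 = 0.937; SE = √(4 × 0.937/120) = 0.177.
- With the period intercept: MS = 0.64 + 0.75 + 0.735 = 2.125; SE = √(4 × 2.125/120) = 0.266. Adding the treatment coefficient at patient level brings it to about 0.31.

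**Where the order of nesting does matter (n = 10, simulated):**

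- *Random treatment slope placed at the patient-in-pair level* (slope SD 1, period SD 0.5, pair SD 0.5, week SD 1, 60 series): SE 0.323, against 0.400 with the slope at patient level. The true value is √[(1/3 + 0.25 + 1)/10] = 0.398.
- *Main effect of a patient-level covariate* (patient SD 1.5, pair SD 0.5, slope SD 1, week SD 1, no period variance, 150 series): SE 0.677 in the stated order against 0.949 in the corrected order, with an empirical SD of 0.926. The stated order treats 10 patients as 20.

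**The case against.** The strongest reply is that this is a slip in one phrase. Turning the order round, with nothing else changed, leaves the SE of the average effect where it was. That stands. A reader might infer that the reversed nesting itself makes the SE too small; the design does not support that. A pair intercept in either order lowers the SE relative to the patient-only model when there is pair or period variance. With pair variance alone, the lower value is the right one (0.183, against 0.212 for patient only).

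Three further points stand in whole or in part.

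- The pair model is not the plan's only use of the pair structure. Pair also enters as a fixed effect in the carryover step, and the individual-trial analysis compares period means within pairs.
- About half of the true variance in the heterogeneity example comes from effects that differ between patients, and the plan already intends to test a term for that. Fitted at patient level with no period term, that coefficient also absorbs much of the period noise: in the two scenarios with period SD 0.8 its simulated SE was 0.307 and 0.309 against a true 0.312. But period noise is then partly read as differences in treatment effect between patients, which the secondary objective sets out to explain. It also does not help the primary model, which has the patient intercept only.
- The article does not say that the treatment slope or the patient-level covariates will be fitted together with the nested pair intercept. The double-counting is therefore conditional.

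**Conclusion.** The stated hierarchy contradicts the design and should be corrected. Taken alone, the reversal has no effect on the SE of the average effect in complete trials with intercepts only. Its harm lies in the variance components, the lost correlation between a patient's two pairs, and double-counting if patient-level terms or the treatment slope are put at that level.

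The understated SE is a matter of the missing period level. It affects the pair model and the primary model alike, and only if period-to-period variance exists. In the heterogeneity example the SE is about 0.18 in either order against about 0.31, a gap due to both unmodelled heterogeneity and the missing period term. All variances and the number of patients are assumptions; with no pair, period or effect variance, all the models agree.

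Severity is minor: the meta-analysis is a secondary, exploratory proof of concept, and decisions for individual patients do not rest on this model.

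**What to change.** Restate the structure as weekly measures within periods, periods within pairs, and pairs within patients. Fit random intercepts for patient, pair within patient, and period within pair. Keep the planned random treatment coefficient at patient level, and judge patient-level covariates against between-patient variation. Carry the period intercept into the primary model as well, since it has the same gap. With only a few trials some variance components may be estimated as zero, and that should be reported when it happens. The cost is one line of analysis wording and of model code; no data collection changes.
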